**Primary Endpoint**

proportion of patients with virological failure (defined as two consecutive measures of HIV-RNA higher than 50 copies/mL or a single measure higher than 1000 copies/mL) within 48 weeks at per protocol analysis (TLOVR), with switch=failure. Switch=stop or drug implementation in MVC+DRV/r arm; the same in control arm

**Secondary Endpoints**

• proportion of patients with virological failure (two consecutive measures of HIV-RNA higher than 50 copies/mL or a single measure higher than 1000 copies/mL) within 96 weeks at intention-to treat analysis with missing value=failure.

• time to virological failure at survival analysis

• proportion of patients with X4 viral tropism at failure (RNA or DNA genotyping)

• proportion of patients with at failure X4viral tropism at failure (RNA or DNA genotyping)

• economic impact of DRV/r+ MVC versus current ART

• modification of IMT and FMD from baseline at 48 and 96 weeks

• modification of bone density from baseline at 48 and 96 weeks

• evolution of CD4 cell count during the 96 study weeks

• modification of metabolic parameters during 96 weeks

• modification of the results of neurocognitive tests from baseline at 48 and 96 weeks

• evolution of maraviroc plasma concentrations during the 96 weeks

• evolution of adherence and quality of life after 24, 48 and 96 weeks

**Statistical analysis and sample size calculation**

Based on the assumption that by continuing the current cART regimen 90% of patients on viralogical suppression will still has an undetectable viral load at 48 weeks, in order to test for non-inferiority of MVC+DRV/r versus maintaining the current cART regimen with the “per protocol” method (delta = -10%, 95% confidence interval, 80% power), assuming a 5% of patients lost to follow-up we will need 165 patients per arm.

- Primary end-point analysis:
- Primary analysis: Time to loss of virolgical response (TLOVR), Per protocol (PP) method: incorrectly randomized patients and patients with major protocol violations will be excluded from the analysis.
- Secondary analysis:
  - Observed: only patients with an available viral load measure will be included.
  - Intent To Treat (ITT) – all randomized patients will be included
    - Switch = Failure (S = F)
    - Switch in patients with undetectable viral load = no failure (S ≠ F)

The time to each endpoint will be evaluated by survival analysis, the differences in laboratory tests will be analyzed by T-test for independent samples or Fisher’s exact test at baseline, tests for paired samples in order to evaluate the changes in specific variables from baseline.

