**Criteria for exit from the study**

Virological failure, defined as the occurrence of 2 consecutive HIV-RNA above 50 copies / mL or a single value greater than 1000 copies / mL.

Diagnosis of opportunistic infection or other HIV-related disease or serious adverse events associated with drugs administered to the patient

Grade 4 laboratory abnormalities at monitoring exams (except for lipids)

Major protocol violations

Withdrawal of informed consent

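### The primary per-protocol analysis does not say whether a major violator who also stops or adds a drug is a failure or is excluded, and the planned ITT analysis has no role in the decision

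*Combined protocol and SAP*

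**What the plan says.** The Primary Endpoint section defines the 48-week endpoint as virological failure at per-protocol analysis (TLOVR) with switch counted as failure, and explains the term: "Switch=stop or drug implementation in MVC+DRV/r arm; the same in control arm".

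The section Statistical analysis and sample size calculation sizes the non-inferiority comparison "with the “per protocol” method" ("delta = -10%, 95% confidence interval, 80% power"). It makes per-protocol TLOVR the primary analysis and states that "incorrectly randomized patients and patients with major protocol violations will be excluded from the analysis". Three further analyses of the primary endpoint are listed as secondary: observed, ITT with S=F, and ITT with S≠F.

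Criteria for exit from the study lists "Major protocol violations" beside virological failure, clinical events and serious drug-related adverse events, grade 4 laboratory abnormalities and withdrawal of consent. Study design states that the trial is open label, and Monitoring has viral load measured at every visit.

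Three things are not stated:
- what a major violation is;
- who classifies violations, when, and with what knowledge of arm and outcome;
- what follows if the per-protocol and ITT results disagree.

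**The concern.** Two rules act on the same analysis set. One turns a stop or added drug into a failure; the other removes major violators from the denominator. Most patients will meet at most one of them. A patient who stops or adds a drug in breach of the protocol, or who exits as a violator and then changes drugs, can meet both. Counting that patient as a failure and excluding that patient are then both consistent with the written plan.

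The choice would be made after randomisation, by people who can know the arm and the viral load. Each failure that becomes an exclusion improves the apparent result of its arm. Because the formal conclusion rests on the per-protocol set, and the all-randomised analysis need not meet the margin, nothing in the plan guards the conclusion against that choice.

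**Working it through.** **1. The plan's own figure.** Inputs from the sample size paragraph: 90% control success, margin 10 points, 95% CI (read as two-sided), 80% power, 5% loss, 165 per arm. Success in the MVC+DRV/r arm is not stated; it is assumed equal, at 90%. The Farrington-Manning formula uses success rates restricted to differ by exactly the margin, here 93.1% and 83.1%:

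- s0 = √(0.931×0.069 + 0.831×0.169) = 0.452; s1 = √(2×0.9×0.1) = 0.424
- n = (1.96×0.452 + 0.842×0.424)² / 0.10² = 154.4, so 155
- 155 / 0.95 = 163.2, so 164, against 165 stated

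The plan names no formula; the unpooled formula gives 142, then 150. The stated size is reproducible and is not the problem. Power is also not very sensitive to exclusions as such: with 5%, 10%, 15% or 20% lost in total, unpooled power is 84%, 82%, 80% or 77%. The issue is bias.

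**2. How few patients matter.** The counts are assumed. Wald 95% CI for success in MVC+DRV/r minus success in control:

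- Control 16/165 failures (9.7%), MVC+DRV/r 24/165 (14.5%): difference -4.8, SE 3.58, lower limit -4.85 - 1.96×3.58 = -11.9. Margin missed.
- Four of the 24 excluded as violators, 20/161 (12.4%): difference -2.7, SE 3.47, lower limit -2.73 - 1.96×3.47 = -9.5. Margin met.
- With 26 failures, excluding six (20/159) moves the lower limit from -13.2 to -9.7.
- In the other direction: control 16/165, MVC+DRV/r 20/165 gives -2.4, SE 3.43, lower limit -9.1 (met). Excluding four control failures (12/161) gives -4.7, SE 3.28, lower limit -11.1 (missed).

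**3. Error rate under assumed rates.** Take virological failure of 8% in both arms and stops of 12% (MVC+DRV/r) versus 2% (control). S=F failure is then 20% versus 10%, a true difference exactly at the margin. If a fraction f of stops in each arm is excluded, the expected per-protocol failure rate is (8 + 12(1-f))/(100 - 12f) versus (8 + 2(1-f))/(100 - 2f). The last column is from simulation (at least 200,000 trials, 165 per arm, Wald 95% CI).

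| Stops excluded | Expected failure, MVC+DRV/r vs control | Difference in success | Non-inferiority declared |
|---|---|---|---|
| 0 (ITT S=F) | 20.0% vs 10.0% | -10.0 | 2.7% |
| 5% | 19.5% vs 9.9% | -9.6 | 3.4% |
| 10% | 19.0% vs 9.8% | -9.2 | 4.3% |
| 25% | 17.5% vs 9.5% | -8.0 | about 8% |
| 50% | 14.9% vs 9.1% | -5.8 | 22% |
| 100% | 9.1% vs 8.2% | -0.9 | 80% |

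The documents give no expected rate of stops or violations, so the range matters more than any one row. Virological failure is equal by construction, so these conclusions are false with respect to the S=F composite, which is the declared endpoint.

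**4. Power if both analyses must meet the margin.** Equal arms, 165 per arm, half of stops excluded from per protocol, virological failures and stops in the ratio 6:4:

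| S=F success | Virological failure + stops | ITT (S=F) alone | Both |
|---|---|---|---|
| 90% | 6% + 4% | 86% | 84% |
| 85% | 9% + 6% | 72% | 69% |
| 80% | 12% + 8% | 62% | 58% |

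**The case against.** The strongest reply is that switch=failure is written inside the per-protocol analysis. If switches were removed as violators, the clause would have nothing to act on. The specific rule should therefore govern, and major violations would mean other departures. The exit criteria point the same way, since they list violations apart from virological failure, drug-related events and withdrawal of consent. This stands for the ordinary case: a stop for toxicity reads as a failure. A reader might infer that every stop or added drug is both a failure and an exclusion, and so quote the 80% error rate. The documents do not say that any stop is a major violation, and excluding all of them would run against the endpoint definition. The 80% row is a worst case. The reply does not settle the patient who meets both rules, because the plan gives no definition and no order of precedence.

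A reader might also infer that the bias must favour MVC+DRV/r. That arm changes regimen at baseline, so more stops there are plausible. But Objectives admits patients with toxicity or a wish to simplify, and controls remain on their old regimen in an open-label trial, so switching could be more frequent among controls. The direction is open.

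Finally, ITT on all randomised patients is prespecified, so a disagreement would be visible. This is correct, and it would be wrong to say that no ITT analysis is planned. Visibility is not a decision rule, however: a per-protocol success beside an ITT failure would still satisfy the plan. The separate ITT endpoint with missing=failure under Secondary Endpoints is at 96 weeks.

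**Conclusion.** The point holds as an unresolved boundary in the primary analysis; it is not a direct contradiction. Major violation is undefined, can arise after randomisation, and can overlap with the switch rule. No precedence or blinded classification is described, and ITT (S=F) carries no weight in the conclusion.

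If 5% to 25% of stops were reclassified, the assumed scenario raises false non-inferiority from 2.7% to between about 3% and 8%; at half it is 22%. Near the margin, four patients can reverse the result in either direction. All of this rests on assumed failure, stop and exclusion rates. The remedy is inexpensive, so this is a cheap improvement.

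**What to change.** 1. In Statistical analysis and sample size calculation, state that any patient in either arm who meets the virological-failure or switch definition of the Primary Endpoint section stays in the per-protocol analysis as a failure and is never excluded as a major violator. List the major violations, and have them classified before analysis without knowledge of arm or outcome.
2. Declare non-inferiority only if the 95% CI excludes -10% in both the per-protocol and the already planned ITT (S=F) analyses at 48 weeks.

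It is not necessary to count every study exit as a failure, which would go beyond the endpoint definition, or to bar all post-randomisation exclusions. Patients who breach the protocol without failing or switching can still be excluded. Because item 1 keeps violators who fail and drops those who do not, it is best adopted together with item 2.

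The cost is wording plus some power. Joint power is about 84% (ITT alone 86%) only if S=F success is 90%; it is about 69% (72%) at 85% and 58% (62%) at 80%. The plan's assumption is that "by continuing the current cART regimen 90% of patients on viralogical suppression will still has an undetectable viral load at 48 weeks", which describes viral suppression. S=F success may be lower, so the sponsor should restate the expected rate and power for the S=F endpoint when making this change. By the unpooled formula, 80% power for ITT alone needs 201 per arm at 85% success and 252 at 80%, before any allowance for loss.

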**Baseline**

The day the simplified therapy with maraviroc, darunavir / ritonavir will be administered for the first time will be defined as baseline (day 0); in the control group the baseline will be represented by the first visit after the randomization . The physical examination should be repeated along with the determination of vital signs, weight and height, blood tests (liver function, including ALT, AST, tot bil / alkaline phosphate and gammagt, and kidney, fasting glucose, complete lipid profile, amylase, lipase, Na, K, P, Ca, CK), the complete blood count, urine examination complete, the lymphocyte immunophenotyping, HIV-RNA, and set aside a plasma sample and a sample of whole blood for 'genotype analysis of V3 on RNA and DNA, respectively. Furthermore, additional analysis will be performed on the bone metabolism (alkaline phosphatase, calcitonin, parathyroid hormone, osteocalcin, dose of vitamin D3, urinary hydroxyproline, urinary hydrossiploline).

Renal function is monitored by calculation of the CG or MDRD and the measured creatinine clearance, 24 hours proteinuria, natriuria, Kaliuria, calciuria, phosphaturia, chlorides and uricuria 24 hours.
Fasting insulin levels will also be assessed at baseline. In specific subgroups subcutaneous fat on the face, arm and thigh will be measured by ultrasound (Liposound); the average intima media thickness (IMT), carotid Doppler ultrasound, endothelial function by flow-mediated dilation (FMD) of brachial artery and bone mineral density and distribution of subcutaneous fat by DEXA will also be measured.

Finally, patients will be asked to complete a self-reported adherence questionnaire, a self-reported questionnaire on symptoms and quality of life and will undergo an evaluation of basic neurocognitive screening tests, and if necessary based on the screening tests, a more in depth evaluation using extensive neurocognitive assessment batteries. On the same day candidates will be subjected to the patients randomized 1:1 in the following arms:

A) * Maraviroc 300 mg (1 tablet) every 24 h + 800 mg darunavir (2 400 mg tabs) every 24 h + ritonavir 100 mg (1 heat stable tablet) every 24 h in the morning (in order to make TDM)
B) Continuation of previously ongoing treatment

* 150 mg (1 tablet) every 24 h if estimated creatinine clearance <80 ml ​​/ min

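### For the CD4, metabolic, bone, IMT/FMD and neurocognitive endpoints, no between-arm comparison of change from baseline is prespecified

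*Combined protocol and SAP*

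**What the plan says.** Under Statistical analysis and sample size calculation, the virological analyses are set out in some detail. Every other outcome is covered by one sentence with three parts:

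- "The time to each endpoint will be evaluated by survival analysis".
- For laboratory values, "the differences in laboratory tests will be analyzed by T-test for independent samples or Fisher’s exact test at baseline".
- For follow-up, "tests for paired samples in order to evaluate the changes in specific variables from baseline".

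The Secondary Endpoints section lists the outcomes concerned as courses or changes over time. Examples are "evolution of CD4 cell count during the 96 study weeks", "modification of metabolic parameters during 96 weeks" and "modification of bone density from baseline at 48 and 96 weeks". IMT and FMD, and the neurocognitive tests, are worded in the same way. None of these entries names a comparator. The economic endpoint in the same list does: it is set against current treatment.

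No section mentions a between-arm test of change, an ANCOVA or a mixed model.

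**The concern.** The Study design section describes a 1:1 randomised controlled trial. The control arm shows what would have happened without the switch, and a paired test within each arm makes no use of it. A within-arm change combines the effect of the regimen with several other things:

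- **Time trend:** drift in CD4, lipids, bone or arterial measures over 48 to 96 weeks.
- **Practice effects:** the neurocognitive tests are given at baseline and repeated at weeks 48 and 96.
- **Regression to the mean:** this applies to patients enrolled because of a toxicity, which is one of several entry reasons given under Objectives.

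With two within-arm p-values per endpoint, the natural next step is to read significance in one arm but not the other as a treatment difference. That is not a test of the difference. It can suggest an effect where there is none, and it gives no estimate of a real one.

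The second objective is to gather information on the safety, immunologic and economic impact of the strategy. The immunologic and safety parts lean on these endpoints. The trial is also open label, so choosing the comparison after the data are seen would weaken it further.

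**Working it through.** **What each named method can do for these endpoints**

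| Method in the plan | Where it applies | Between-arm comparison of change? |
|---|---|---|
| Survival analysis | Time to an endpoint | No: a continuous change has no defined event |
| Independent t-test or Fisher's exact test | Laboratory differences, at baseline | No: randomisation makes any baseline difference chance |
| Paired tests | Change from baseline | No: within patient, hence within arm |

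The plan states no numerical figure for these endpoints, so there is none to reproduce. The only plan figures used below are the 165 per arm and the 5% loss, which give 165 × 0.95 = 156.75, about 157 evaluable per arm.

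**How often contrasting two paired tests misleads**

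Let both arms have the same true mean change d, in units of the SD of the change, and test each arm at two-sided 5%. The power of one paired test is

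p = Φ(d√n − 1.96) + Φ(−d√n − 1.96).

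The arms are independent, so the chance that exactly one is significant is 2p(1 − p). With n = 157:

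| Common change d (SD) | d√n | p | 2p(1 − p) |
|---|---|---|---|
| 0 | 0 | 0.050 | 9.5% |
| 0.10 | 1.253 | 0.240 | 36.5% |
| 0.157 | 1.967 | 0.503 | 50.0% |
| 0.20 | 2.506 | 0.708 | 41.4% |
| 0.30 | 3.759 | 0.964 | 6.9% |

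A direct between-arm test would be significant 5% of the time in every row. The expression 2p(1 − p) cannot exceed 50%, and it reaches that where p = 0.5, at about d = 1.96/√n. Here that is 1.96/√157 = 0.156 SD.

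DEXA, IMT, FMD and the neurocognitive tests are done in selected centres, with no patient numbers given. Under assumed sizes of 30, 50 and 82 per arm, the same 50% maximum moves to 0.36, 0.28 and 0.22 SD.

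**What a direct comparison could detect**

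For 80% power at two-sided 5%, the detectable between-arm difference is (1.96 + 0.842)√(2/n) SD of change. That is 0.32 SD at 157 per arm. At the assumed 30, 50 and 82 per arm it is 0.72, 0.56 and 0.44 SD.

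**Gain from adjusting for baseline**

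With equal variances at both times and baseline–follow-up correlation r, the variance ratio of ANCOVA to a comparison of raw changes is (1 − r²)/(2(1 − r)) = (1 + r)/2. This is 0.75 at r = 0.5 and 0.90 at r = 0.8. It is a gain in efficiency and does not show an error in the plan.

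**The case against.** **The sentence is ambiguous.** The words on baseline could attach to Fisher's test alone. That would leave an independent t-test of laboratory differences at unstated times, which could cover CD4 and metabolic values. This reading is possible but less natural. It would not reach bone density, IMT/FMD or neurocognitive tests, which are not laboratory tests, and it would still leave the time points and the estimate undefined.

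**Nobody plans to contrast the two p-values.** This is correct. The table shows what happens if someone does, and 50% is its mathematical ceiling, not a typical rate. The main defect, that no between-arm comparison is named, does not depend on it.

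**These are secondary endpoints with no hypothesis or sizing.** This stands, and it limits the severity.

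**Stronger readings that the documents do not support.** A reader might infer that the trial compares its arms only at baseline. It does not: virological failure is compared after baseline, and the economic endpoint is worded as a comparison. A reader might also infer that the trial could never answer these questions. The data would allow a comparison, since both arms follow the same visit schedule; what is missing is its prespecification. Nor does the second objective mention metabolic outcomes, which appear in the list of secondary endpoints. Finally, toxicity is not a condition of entry under Eligible subjects, so regression to the mean concerns only some patients.

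**Conclusion.** The concern holds for the continuous secondary endpoints measured in both arms: CD4, metabolic parameters, bone density, IMT/FMD and neurocognitive tests. On the natural reading, the stated method for change from baseline leaves the control arm unused, and no between-arm analysis is prespecified. It should be fixed, but it does not threaten the trial's main conclusion, because the primary non-inferiority analysis and the 165 per arm are untouched.

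If paired results were set against each other under equal true change, exactly one arm would be significant between 6.9% and 50% of the time over common changes of 0 to 0.30 SD, against 5% for a direct test. This assumes about 157 evaluable per arm, normal approximations and two-sided 5% tests. The documents give neither SDs nor substudy sizes, so the figures show the order of the problem and do not predict results.

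**What to change.** In Statistical analysis and sample size calculation, replace the part of the sentence on t-tests and paired tests with wording such as:

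*For each continuous secondary endpoint measured in both arms, the arms are compared at weeks 48 and 96 by ANCOVA with arm as factor and the baseline value as covariate, or by a mixed model over the scheduled visits. The adjusted between-arm difference is reported with its 95% CI. Endpoints measured only in selected centres are analysed within that subset. Baseline values and within-arm changes are summarised descriptively.*

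Three details belong with it:

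- Maraviroc concentrations must be excluded, because the flow chart schedules drug-level monitoring in arm A only.
- For the neurocognitive endpoint, the compared score should come from the tests given to all patients assessed. The fuller evaluation is done only "if necessary based on the screening tests, a more in depth evaluation using extensive neurocognitive assessment batteries", so it is not available for everyone.
- The analysis set and the handling of missing values should be stated. Virological failure is a criterion for leaving the study, so later values may be missing selectively.

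The cost is plan wording only. The measurements are already scheduled in both arms, and no visits or patients are added.

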**Study assessment and procedures**

**Screening visit**

During screening visit will be obtained written informed consent, patients medical history collection and treatment (antiretroviral or not) with complete registration of all concomitant medications, the search for markers of HBV and HCV infection, pregnancy test for women of childbearing age or serum FSH dose for women in menopause for less than 2 years, complete physical examination of vital signs, weight and height, blood tests (liver and kidney function, fasting glucose, complete lipid profile, amylase, Na, K, P , Ca, Cl, CK, uric acid), complete blood count, complete urinalysis, lymphocyte immunophenotyping, HIV-RNA. Will also be determined the genotypic tropism of HIV-V3 from viral DNA extracted from whole blood by sequencing.

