**Monitoring**

The monitoring visits will be organized at 4, 12, 24, 36, 48, 60, 72, 84 and 96 weeks.
At each visit monitoring will include blood chemistry tests (all lipids, transaminases, tot/conjugated bilirubin, amylase creatinine, Na, K, P, CK, fasting glucose, plasma) and blood cell counts, urinalysis, lymphocyte subsets and viral load of HIV, monitoring of plasma concentrations of maraviroc, darunavir and ritonavir at 24 + / - 2h (NB patients in arm A should be instructed not to take the study medication prior to sampling).
Monitoring of renal function by MDRD or CG will be repeated at all visits, while the creatinine clearance, proteinuria of 24 hours, natriuria, Kaliur, calciuria, phosphaturia, chlorides and uricuria of 24 hours will be measured at week 24, 48 72 and 96.
The assessment of fasting insulin and markers of bone metabolism (alkaline phosphatase, calcitonin, parathyroid hormone, osteocalcin, vitamin D, calciuria and phosphaturia urinary hydroxyproline) will be repeated at 24, 48 and 96 weeks, measuring subcutaneous fat on the face, arms, thighs and the average intimal thickness (IMT) and DEXA for bone densitometry will instead be repeated at 48 and 96 weeks. The questionnaire on self-reported adherence will be repeated at each visit; the questionnaire on self-reported symptoms and quality of life will be administered to 4, 24, 48 and 96 weeks, while the assessment of neurocognitive tests (battery of screening tests for investigation and possible pathological) will be repeated at week 48 and 96.
In case of virological failure (occurrence of 2 consecutive HIV-RNA above 50 copies / mL or a single value greater than 1000 copies / mL) a genotypic resistance test on plasma viral RNA will be performed within one month from the observation. At each visit, a plasma sample for the V3 genotype and resistance to HIV and a sample of whole blood for analysis of viral DNA will be stored for possible future evaluation as judged by the principal investogator of the study. The flow chart of the visits is attached to the document (Annex 1). Blood chemistry, hematology and microbiological studies will be performed under the clinical routine and without additional costs for the structure.
The therapeutic plasmatic drug monitoring will be carried out in collaboration with the Institute of Pharmacology (Clinical Pharmacology Service) of the Gemelli Hospital.

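### CD4, glucose, lipids and other chemistry are measured twice before treatment, but the planned analysis appears to use one value and makes no baseline adjustment, which gives up a modest amount of precision

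*Combined protocol and SAP*

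**What the plan says.** The section on statistical analysis and sample size attaches the independent-samples t-test and Fisher's exact test to baseline. For change it plans "tests for paired samples in order to evaluate the changes in specific variables from baseline". It does not say which variables these are, and it names no covariate and no repeated-measures model.

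The Baseline section fixes one visit per arm. In the switch arm the day of first dosing "will be defined as baseline (day 0"); for controls, "in the control group the baseline will be represented by the first visit after the randomization".

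The Screening visit section already collects "blood tests (liver and kidney function, fasting glucose, complete lipid profile" and further chemistry, together with "lymphocyte immunophenotyping, HIV-RNA". The flow chart places this visit at day -28 and shows lymphocyte subsets, HIV-RNA and chemistry again at day 0. Fasting insulin and the bone-metabolism panel first appear at day 0.

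The Secondary Endpoints list gives CD4 and metabolic parameters as their course over 96 weeks, without naming a baseline or particular visits. For IMT and FMD, bone density and neurocognitive tests it does say that change is taken from baseline.

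**The concern.** A single CD4 count or lipid value carries biological and assay variation. If change is taken from one such value, all of its noise enters every patient's result. A second pre-treatment value is in the database for every patient screened under the protocol, and no stated analysis uses it.

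Safety and immunological impact are stated objectives, and low metabolic impact is part of the rationale for the regimen. The documents give no power calculation for these endpoints, so their precision depends on a sample size set for virological failure and on how efficiently the data are analysed. At stake is the width of the intervals for CD4 and metabolic parameters. The validity of the trial is not in question.

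**Working it through.** **The plan's own figure.** The only sample size is 165 per arm, for virological non-inferiority. With 90% in both arms (the plan states it for control only), a 10-point margin, one-sided 0.025 and 80% power, the Farrington-Manning variance gives 154.4, so 155; 155/0.95 = 163.2, so 164 per arm. That agrees with 165 to within one patient. The point here does not depend on it. There is no stated figure for CD4 or metabolic endpoints to reproduce.

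**Inputs.** Two pre-treatment values (Screening visit, Baseline, flow chart). The rest is assumed: equal SD at all visits (set to 1), correlation b between screening and day 0, and correlation f between each of these and a follow-up value.

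**Change score.**
- One baseline value: variance = 2 - 2f.
- Mean of two: variance = 1 + (1 + b)/2 - 2f.
- Relative cut = (1 - b)/[4(1 - f)], which is 25% when b = f.

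**ANCOVA.**
- One baseline covariate: residual variance = 1 - f².
- Mean of two as covariate: residual variance = 1 - 2f²/(1 + b).
- Relative cut = 1 - [1 - 2f²/(1 + b)]/(1 - f²).

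| f (with follow-up) | b (screening with day 0) | Cut, change score | Cut, ANCOVA |
| --- | --- | --- | --- |
| 0.5 | 0.5 | 25% | 11.1% |
| 0.7 | 0.7 | 25% | 17.0% |
| 0.9 | 0.9 | 25% | 22.4% |
| 0.5 | 0.7 | 15.0% | 5.9% |
| 0.6 | 0.8 | 12.5% | 6.3% |
| 0.7 | 0.8 | 16.7% | 10.7% |
| 0.7 | 0.9 | 8.3% | 5.1% |
| 0.8 | 0.9 | 12.5% | 9.4% |

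Example, f = 0.7 and b = 0.9. Change score: 0.55 against 0.60, a cut of 8.3%. ANCOVA: 1 - 0.98/1.9 = 0.484 against 0.51, a cut of 5.1%.

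**What this means for an interval.** The ANCOVA variance ratios run from 0.949 to 0.776. Their square roots are 0.974 and 0.881, so intervals become about 3% to 12% narrower. An effect with 80% power would have Φ(2.80/0.974 - 1.96) = 82% to Φ(2.80/0.881 - 1.96) = 89%.

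**Adjustment itself.** For a between-arm contrast with one baseline value, ANCOVA against an unadjusted change score has variance ratio (1 - f²)/(2 - 2f) = (1 + f)/2. That is 0.75 at f = 0.5, 0.85 at 0.7 and 0.95 at 0.9. This gain is separate from the gain of the second value.

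**The case against.** The strongest reply is that nothing here is an error. Day 0 is the conventional baseline, these are secondary endpoints, and the Baseline section dates a visit without forbidding use of the screening value. The endpoint list does not tie CD4 or metabolic parameters to baseline, and the statistical section does not say which variables get paired tests. All of this stands, so the single baseline is the natural reading and not a stated rule. It does not remove the point, because no analysis in the documents uses the screening value or adjusts for baseline.

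A second objection concerns selection, and it also stands. The exclusion criteria apply limits on estimated GFR and transaminases at the screening visit, and the CD4 limit may act there too, since the section does not say which value it uses. Adding a selected value to a within-arm paired change can shift that change by regression to the mean, and a control arm does not correct a within-arm test. A between-arm comparison adjusted for that value is not biased in this way, because the limits are applied before allocation.

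Three stronger readings are tempting, and the documents do not support them:

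- **A fixed 25% saving whatever the correlation.** This needs equal correlation between all visits. Screening and day 0 are about four weeks apart while follow-up runs to 96 weeks, so the two early values may well correlate more with each other. The 25% also belongs to the change score and not to an adjusted model.
- **The same waste for adherence.** The endpoint is "evolution of adherence and quality of life after 24, 48 and 96 weeks", while "The questionnaire on self-reported adherence will be repeated at each visit", which is nine monitoring visits. But the endpoint is a time course, and a mean over all visits would answer a different question. Virological failure is also a criterion for leaving the study, so patients would contribute different numbers of visits, possibly related to adherence.
- **Biased CD4 or metabolic results.** A single day-0 baseline costs precision and does not by itself bias the comparison of arms.

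**Conclusion.** The point holds as a minor, inexpensive improvement to secondary analyses. CD4, fasting glucose, lipids and other chemistry have two pre-treatment values, and the plan as naturally read uses one and makes no baseline adjustment. The second value is worth about 5% to 22% of ANCOVA variance, or about 8% to 25% of change-score variance.

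These ranges rest on assumed correlations, equal SDs, and screening and day 0 being equally correlated with follow-up. If the screening value tracks follow-up less well than day 0 does, the gain is smaller. The primary endpoint and the sample size are untouched.

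**What to change.** In the section on statistical analysis and sample size:

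- Compare the arms on CD4, and on each metabolic parameter measured twice before treatment, with a baseline-adjusted model: ANCOVA, or a repeated-measures model on the collected visits.
- Use the mean of the screening and day-0 values as the baseline covariate, or day 0 alone if screening is missing.
- Keep day 0 alone as the baseline for any within-arm paired change, for the selection reason given above.
- State that parameters without a screening value, such as fasting insulin and the bone-metabolism panel, use day 0 only.

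The choice should be fixed before outcome data are seen, so that the baseline definition cannot depend on the results. The cost is a small addition to the analysis model: the plan currently names no adjusted model and, as naturally read, no between-arm test of change, so a short paragraph is needed. No visit, sample or patient is added.
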